#### Non-linear Pedagogy

Ecological dynamics considers individuals (or at a higher level of analysis, a class of children) to be complex and adaptive systems (Davids et al., 2012). If this theoretical premise is accepted there is, from a learning design perspective, considerable uncertainty as to how any particular PE lesson will unfold, and consequently lesson plans should act as a guide, rather than being adhered too strictly at the cost of learning opportunities. Coaches therefore need to adopt a frontloaded approach, whereby they consider in advance how any changes within the PE lesson may alter the learning of each child. While this may seem like an impossible task, there are some consistent variables across schools (e.g., class sizes, lesson duration, national PE curriculum objectives). Moreover, within the classroom there will be common constraints acting upon children such as their age, socio-economic demographic, and the school environment, which either facilitate or hinder motor learning. The research team and coaches will work together to identify common constraints for year 1 children, creating an expected range of variation that the coach could plan for and exploit during their PE lessons, allowing them to design more individualized and meaningful movement experiences for their children. It is important to highlight that this approach recognizes that it is impossible to repeat a movement identically from one attempt to the next (Newell, 1986). Thus, accepting variability in movement is central and the coaches’ role is to encourage participants to adapt their movements and continue to improve their technique.

In order to help the coaches deliver the Non-linear Pedagogy curriculum, they will be trained to utilize two models: Newell’s (Newell, 1986) model of motor learning, and the Space, Task, Equipment and People (STEP) framework (Youth Sport Trust, 2018). Newell (1986) model of motor learning is based on Ecological Dynamics and will be used to teach coaches that high movement competence is represented by a child’s ability to be creative and adaptable whilst succeeding in their performance of movement skills. Coaches will be trained to identify if children’s movement behaviors are in the coordination, control or skill stage of learning, and subsequently individualize the PE activity toward a child’s particular level of competence by changing one or more task constraints. The STEP framework (Youth Sport Trust, 2018) will support the manipulation of task constraints by increasing or reducing the likelihood of affordances, with the aim of enabling children to effectively solve movement problems.

Alongside these models, the Non-linear Pedagogy curriculum is underpinned by five core pedagogical principles:

(1)A representative learning design. Arguably, a common representative learning design for young children within a PE setting is fun (Headrick et al., 2015; Beni et al., 2017; Foweather and Rudd, 2020). Representative learning design also highlights the importance of skill transfer between multiple settings. For this to occur, it is important that there is a behavioral correspondence between learning and the child’s other performance environments, such as the playground, afterschool clubs and sport clubs.(2)Movement-perception coupling must be maintained when performing skills. This means that skills are practiced in their entirety rather than broken down into component parts or in decontextualized fashion. Movement-perception coupling is seen as a micro (skill level) equivalent of the macro (environment) representative learning design. From a macro perspective, the movement-perception coupling is maintained, for example, within gymnastics lessons by having all equipment present throughout the duration of each lesson, improving their ability to self-regulate their behavior. At the level of the microstructure of practice, the coach does not prescribe the type of movement skill that the child should learn. Instead, the coach promotes creativity and exploration through the use of scenarios and/or mini-games that encourage children to explore and experiment with a broad range of movement skills, meaning movements are learnt in context, and the coach does not isolate skills or develop them by separating into components. Alongside this the coach employs the use of analogies and open-ended questions in the effort to encourage problem solving from the child rather than telling the child exactly what to do.(3)An external focus of attention is considered necessary to support the acquisition of both creative and functional movement skills. Profeta and Turvey (2018) suggest that if the learner allocates attentional resources to the task and environment rather than to the own movements, movement coordination and control is delegated to the lower levels of the central nervous system where movement is less conscious and learning occurs implicitly. An external focus of attention allows for self-organization of movement patterns to meet the goal of the task, whilst an internal focus of attention promotes a conscious process which is believed to lead to an undesirable breakdown of movements (Wulf, 2007; Chow et al., 2016). To develop functional and adaptive movements, coaches were trained to create mini-games within the lessons, and to utilitize and build upon teaching methods such as analogies and questions. These type of activities create an external focus of attention.(4)The application of constraints – boundaries or features that encourage the development of movement competence. There are three types of constraint: individual, environmental, and task (Pesce et al., 2016b). The coaches are able to make decisions on what task constraints to manipulate based upon their observations of children’s interactions with their environment and using their knowledge of Newell’s stages of learning and the STEP framework (Newell, 1986; Youth Sport Trust, 2018). For example, the coach could reduce or increase the playing Space, alter the rules of the Task, use different sized Equipment and/or change the number of People playing the game.(5)Infusing perturbations within the learning process. This means that if the coach observes a child demonstrating a stable and functional movement skill, the coach will act to destabilize the skill by altering task constraints or changing the task goal. Changing task constraints will result in new affordances. It is important that the coach understands that it is acceptable for different children to display different movement solutions to the same task and that regression in skill is inevitable when altering constraints (such as equipment). As long as the skill is functional and achieves the outcome of the lesson, then it is to be accepted as a pertinent solution.

The Non-linear Pedagogy PE curriculum was successfully trialed with year 1 children across three primary schools in summer 2016. A copy of the lesson plan can be found in Supplementary File 2.

#### Control (*n* = 6 Schools)

Control schools will be asked to continue with their usual PE curriculum provision, and timetable and deliver 2 × 60 min PE lessons per week for 15 weeks. The control schools follow current national curriculum aims for PE in Key Stage 1 (early primary), which state that: *‘Pupils should develop fundamental movement skills, become increasingly competent and confident and access a broad range of opportunities to extend their agility, balance and coordination, individually and with others. They should be able to engage in competitive (both against self and against others) and co-operative physical activities, in a range of increasingly challenging situations’* (Department for Education, 2013). Information pertaining to the PE curriculum being delivered in control schools will be collected as part of a process evaluation (described later in secondary outcomes).

### Outcomes

Trained research assistants will undertake 2–3 days of data collection at participating schools across three time-points (see Figure 1). Demographic characteristics including child’s age, gender, ethnicity, and home postcode (used to classify children into deciles of deprivation level using the English indices of deprivation: Ministry of Housing Communities Local Government, 2018) will be collected at baseline through parent consent forms. A number of primary and secondary outcomes are measured through the study.

#### Primary Outcome

##### Movement competence

Movement competence will be assessed through a battery of assessments to examine both technical movement proficiency and movement creativity across different domains (locomotor, object-control, and stability skills). All movement competence assessments will take place during school hours within the school hall or playground and video-recorded for later analysis. Trained research assistants who have established acceptable agreement (80%) in terms of intra-rater and inter-rater reliability with pre-coded videos, will complete analysis of video recordings.

Movement proficiency (technique) will be assessed using the Test of Gross Motor Development-3 (TGMD-3; Maeng et al., 2016) and the Test of Stability Skills (Rudd et al., 2015). Specifically, six locomotor (run, gallop, hop, skip, horizontal jump, slide) and seven object-control (two-hand strike, one-hand strike, one-hand dribble, two-hand catch, kick, overhand throw, underhand throw) skills will be assessed using the TGMD-3 (∼30 min to complete). Proficiency at stability skills will be assessed using the three tasks (log roll, rock, back support) from within the Test of Stability Skills (∼15 min to complete). The psychometric quality of these assessments has been well-established (Rudd et al., 2015; Maeng et al., 2016). Participants will receive a verbal explanation and single demonstration from the assessor and are then given one practice attempt before undertaking two trials of each skill.

Movement creativity will be assessed using the Divergent Movement Ability Assessment (Cleland, 1990), which requires children to complete three stations, a stability skill station, a locomotor skill station and object control skill station (∼15 min to complete). In the stability station, children are asked to make as many shapes on or around the bench as they can. In the locomotor station, children are challenged to find as many different ways to move around the obstacle course as possible. Finally, in the object-control skill station, children will be asked to play with a large ball in a designated area, showing all the different skills and ways that they can play with the ball. For every station, children will complete two 90 s trials, during which, every 30 s the child will get a predefined prompt from the research assistant to support and encourage the child.

#### Secondary Outcomes

##### Physical activity

Participants will be asked to wear a monitor (accelerometer; ActiGraph GT9X, ActiGraph, Pensacola, FL, United States) on their non-dominant wrist continuously for 7 days to measure physical activity at each time point. Participants will be asked to wear their monitors at all times, and to remove them only for water-based activities. Accelerometers will be initialised at a sampling frequency of 30 Hz. During the monitoring period, children’s parents are asked to keep a diary in order to record any times when the monitor is taken off, any activities completed whilst the monitor is removed (e.g., swimming, bathing), and the time the monitor is put back on. A member of the research team will return to the school at the end of the 7-day period to collect the monitors and diaries. Accelerometry data will be used to examine within school, leisure (after-school and weekend), and habitual (total) physical activity levels. Children will be included in the analyses if they have worn the monitor for at least 10 h per day over 3 days, including one weekend day. Time spent in sedentary, light, moderate and vigorous activity will be determined using age- and- population-specific raw acceleration cut-points for the wrist-worn ActiGraph, developed through an ongoing research study (Crotti et al., 2020).

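### A single accelerometer wear rule that requires a weekend day governs every activity analysis, so children with full school-day data are needlessly dropped from the within-school outcome

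*Protocol article*

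**What the plan says.** The Physical activity paragraph under Secondary Outcomes asks children to wear a wrist accelerometer "continuously for 7 days to measure physical activity at each time point". It then defines what the data are for: "Accelerometry data will be used to examine within school, leisure (after-school and weekend), and habitual (total) physical activity levels". The next sentence gives the only wear criterion in the article. Children enter the analyses if they wore the monitor for "at least 10 h per day over 3 days, including one weekend day". The sentence refers to the analyses in general and does not distinguish the three outcomes. No minimum number of school days, and no minimum wear within school hours, is given for the within-school outcome.

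The Data Analysis section says that analyses follow intention-to-treat. The Sample Size section gives an average class size of about 20 and an ICC of 0.16, the latter for movement competence.

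**The concern.** An inclusion rule should ensure that each child has enough data in the window being analysed. The stated rule suits habitual activity, where weekdays and weekends both contribute. It does not suit the within-school outcome, for two reasons.

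- The weekend condition concerns days on which within-school activity cannot occur. It removes children whose within-school data are complete.
- The 10 h is counted over the whole day. It neither requires wear during school hours nor accepts a day with full school-hours wear and little wear at home.

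Physical activity is a named objective and part of a directional hypothesis, and the within-school outcome is one of its three stated forms. At stake are some precision on that outcome and an analysis sample selected after randomization by what families did at the weekend. The rule applies at all three time points, so the loss can recur at each.

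**Working it through.** No figure in the article depends on the wear rule, so there is nothing to reproduce. The check has two parts: the logic of the rule, and the size of the loss under stated assumptions.

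**Logic of the rule**

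| Child's wear | Meets the rule? | Usable for within-school activity? |
|---|---|---|
| Five days of at least 10 h, all school days, complete in school hours; no valid weekend day | No | Yes |
| School hours only, every school day | No, if the school day is 6–7 h (assumption): short by 10 − 7 = 3 h to 10 − 6 = 4 h per day | Yes |
| Three days of at least 10 h, one at the weekend | Yes | Not assured, since no school-hours wear is required |

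**Share of children lost**

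The article gives no weekend compliance. Let p be the chance that a given weekend day is valid. A child with complete school days fails the rule with probability (1 − p)² if the two weekend days are independent, or 1 − p if they are fully correlated.

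- p = 0.9: 1% (independent) or 10% (correlated)
- p = 0.7: 9% or 30%
- p = 0.5: 25% or 50%

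A loss of 15% to 40%, that is 60% to 85% retained, is taken as the working assumption. It lies inside this wider range.

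**Effect on the standard error**

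Inputs from the Sample Size section are m = 20 per class, ICC = 0.16 and the correction factor 1 + (m − 1) × ICC. The 20 children are assumed to have valid school days, losses are assumed even across classes, and the number of classes is unchanged. The variance of an arm mean is then proportional to [1 + (m − 1) × ICC] / m.

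- m = 20: (1 + 19 × 0.16)/20 = 4.04/20 = 0.202
- m = 17 (85% retained): (1 + 16 × 0.16)/17 = 3.56/17 = 0.209; SE ratio √(0.2094/0.202) = 1.018
- m = 12 (60% retained): (1 + 11 × 0.16)/12 = 2.76/12 = 0.230; SE ratio √(0.230/0.202) = 1.067

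The standard error therefore widens by about 2% to 7%. At the extremes of the wider range:

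- 1% lost: m = 19.8, 4.008/19.8 = 0.2024, ratio 1.001
- 50% lost: m = 10, 2.44/10 = 0.244, ratio 1.099

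**Sensitivity to the ICC**

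The article gives no ICC for physical activity.

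- ICC = 0.05 (assumption): 1.95/20 = 0.0975; 1.80/17 = 0.1059, ratio 1.042; 1.55/12 = 0.1292, ratio 1.151. That is 4% to 15%.
- ICC = 0 (independent children): 1/√0.85 = 1.085; 1/√0.60 = 1.291. That is 8% to 29%, the upper bound for this range of retention.

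**The case against.** A common sample is a defensible choice. It lets the three outcomes be compared on the same children, and separate criteria give that up. This stands as a real cost, but reporting the common sample as a sensitivity analysis meets most of it.

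The within-school outcome is also not the whole test of the intervention. T1 falls after delivery ends, activity in observed PE lessons is measured separately in the process evaluation, and the intended benefit extends to play and clubs outside school. That is fair, and it limits the importance of the point. It does not make weekend wear relevant to activity at school.

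Four stronger readings are tempting, and the article does not support them.

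- **A loss of precision of 8% to 29%.** This treats children as independent. The trial is clustered, and losing children within classes leaves the number of classes unchanged.
- **Bias in the treatment comparison.** If weekend wear is unrelated to within-school activity, exclusion costs precision only. Nothing in the article shows that weekend wear differs by arm. Bias cannot be ruled out, since allocation is not blinded to researchers, teachers and coaches, but it is not demonstrated.
- **Sleep counting towards the 10 h.** Monitors are worn at all times and no waking window is stated, so a reader might infer this. The article is silent on the matter. Sleep detection and waking windows are processing details that a condensed article commonly leaves to a fuller document.
- **A within-school value resting on one school day.** This needs the rule to mean at least one weekend day. It can equally be read as two weekdays plus one weekend day.

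**Conclusion.** The point holds in a limited form. As written, the rule excludes children from the within-school outcome for lack of data that the outcome does not use, and it does not ensure wear during school hours. This is a stated criterion that fits one of its stated outcomes badly, not a detail left for later, and nothing else in the article repairs it.

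The size is modest. With 60% to 85% of otherwise usable children retained, the within-school standard error is about 2% to 7% wider. That rests on an assumed compliance range, an even loss across classes and an ICC borrowed from movement competence. A lower ICC, or losses concentrated in a few classes, would move the figure towards the 8% to 29% bound. Selection on weekend behaviour at home after randomization sits uneasily with the intention-to-treat statement and does not depend on these figures. The change is worth making because it is cheap.

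**What to change.** State the wear criteria by outcome:

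- **Within school:** a minimum number of school days with adequate wear during school hours, both fixed before the data are analysed, and no weekend condition.
- **Habitual:** keep the present rule of 10 h over 3 days including one weekend day.
- **Weekend part of leisure:** keep a requirement for weekend wear.
- **Sensitivity analysis:** repeat the within-school analysis in the common sample that meets the present rule, and report by arm how many children each rule excludes at each time point.

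If the present rule was meant for habitual activity only, one sentence saying so is still needed, together with the within-school criterion.

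The cost is a few lines of text and some reprocessing of accelerometer files that are collected anyway. The downside is that the outcomes no longer share one primary analysis sample.

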##### Perceived competence

Perceived physical competence (higher order construct) will be assessed using the corresponding subscale within The Pictorial Scale of Perceived Competence and Social Acceptance for Young Children (Harter and Pike, 1984). The Physical Competence subscale includes items 3, 7, 11, 15, 19, and 23 from the overall Pictorial Scale, and takes approximately 3 min to complete. Each item is scored on a four-point scale, where 4 represents the highest degree of perceived competence. The subscale score is computed by adding values of child responses and ranges from 6 to 24.

Perceived Skill Competence (lower order construct) will be assessed by the Pictorial Scale of Perceived Movement Skill Competence for Young Children 3rd Edition (Harter, 1978; Barnett et al., 2015). The Scale consists of 13 items with two subscales of six and seven items for “Locomotor Skill Perceived Competence” and “Object-Control Skill Perceived Competence,” respectively. Each item is scored on a four-point scale, where 4 represents the highest degree of perceived competence. Subscale scores are computed by adding values of child responses and range from 6 to 24 for locomotor and 7 to 28 for object control (higher values indicate higher perceived competence). All 13 items are summed to generate the Perceived Movement Skill Competence scale score, which ranges from 13 to 52 (higher values indicate higher perceived competence). The Pictorial Scale of Perceived Movement Skill Competence for Young Children is a valid and reliable instrument to assess perceived movement competence in young children (Barnett et al., 2015), taking around 5–7 min to complete.

##### Motivation and psychological needs satisfaction

Self-determined motivation and psychological needs satisfaction are difficult to assess in young children as traditional self-report measures are not appropriate (Sebire et al., 2013). Therefore, following Noonan et al. (2016) and Parker et al. (2018), we have developed a child friendly and age-appropriate Physical Education Motivation Assessment Tool (MAT-PE) to assess self-determined motivation for PE (Fitton-Davies et al., Unpublished). All children in each year 1 class will be asked to draw a picture of “what they like about PE” on one side of a piece of A4 paper and conversely “what they don’t like about PE” on the other. Due to the time necessary to administer and analyze MAT-PE, a random sub-sample of participants (∼*n* = 5 per class) will be selected to participate in 1:1 activities with a researcher. This random sample will be selected from a pool of research children, whom the class teacher will have identified as wishing to talk to researchers, and with a sufficient level of English verbal skills to be able to have a conversation with an adult. The 1:1 activities will take place in a quiet open space outside of the classroom (e.g., school library) where the researcher can be overlooked but not overheard and the conversation between the child and researcher will be recorded using a Dictaphone. The 1:1 activities will commence with an icebreaker activity to relax and build rapport between the researcher and child (a PE themed pair-matching card game). The researcher will then ask the child to describe their drawing(s) and ask questions in order to ascertain information about the picture stimulated from its content. This will be followed by a series of activities including the use of resource cards to explore needs satisfaction during PE lessons in relation to (i) relatedness, (ii) competence, and (iii) autonomy (Ryan and Deci, 2000). The final activity will involve each child being presented with a picture that represents each level of regulation along the self-determined motivation continuum that is coupled with a stem (e.g., ‘*I do PE because it is fun’*). Each stem will be read aloud to the child and clarification given if needed. The child will then be asked to pick their favorite reasons for taking part in PE, which they are subsequently asked to rank (first being most important to them, last being least important). Each 1:1 session will last around 15–20 min. Audio recordings will be transcribed and content analysis will be conducted through the use of a codebook so as to determine changes in basic psychological need satisfaction and self-determined motivation. Thematic analysis will also be conducted so as to capture information from the children around their PE experiences which may have been impacted by the intervention.
